### Randomization

The study statistician generated and administered a blocked 1:1 allocation randomization arrangement for the 16 study hospitals. We did not stratify hospitals by procedure-volume or teaching status since previous research in Ontario indicates that such hospital characteristics do not differentiate patient outcomes following colorectal cancer surgery [40,41]. Following the randomization of an intervention arm site, no further hospital was randomized until that site participated in a workshop (the first component of the QIRC strategy). This was done since patients were immediately accrued following site randomization, despite the typical requirement of 2–4 weeks to arrange a workshop with all or at least a majority of the surgeons at the respective site.

### Data gathering

Data are being collected for patients in the intervention and control groups in identical ways. Primary outcomes data are collected via chart review for at least 30 months, and thus follow-up will be greater for all but the final patients enrolled in the trial. This follow-up period will allow identification of local recurrence events, since local recurrence typically occurs within two years of surgery [1-3]. Hospital charts are reviewed within two weeks of surgery and every three months thereafter. Regional Cancer Centre charts are also reviewed to optimize the collection of data on potential patient treatments (e.g., radiation therapy) and outcomes (e.g., local recurrence). In Ontario, all radiation therapy is delivered at a small number of such Cancer Centres. Quality of life and bowel, bladder, and sexual function were measured at four times: baseline (pre-operatively or within 4 weeks of surgery) and at 6, 12 and 18 months post-surgery. Trained assessors obtained data for secondary outcomes during telephone interviews. All data will be handled with strict confidentiality, and study reports or presentations will maintain patient, surgeon, and hospital anonymity. Data collection will be complete by the end of 2007.

### Analysis

We will use the intention-to-treat principle to analyse data. We will use multiple imputation to handle missing data [42]. Treatment arms will be compared with respect to potential covariates using continuous and categorical univariable analyses. This will include patient (age, sex, comorbidities, weight and height), treatment (adjuvant therapies), tumour (stage, node counts, margin status, other histology measures), and hospital (teaching status, procedure volume) level variables. Methods of analysis, including adjustment for covariates, will use the cluster randomization trial design [38,39]. Specifically, the primary outcomes of colostomy rate and local recurrence rate will be assessed using a nested (cluster) analysis model that will consider the correlation of outcomes within each hospital, and the influence of covariables. Adjustments for adjuvant therapies are especially important since it is likely these treatments will not be delivered among centers using a standard regimen. The major design factor will be arm of study (experimental or control). No adjustment will be made for multiple comparisons of primary outcomes since each is of interest on its own. Secondary analyses will be conducted on bowel, bladder and sexual function, and quality of life using nested analysis of variance. We will conduct analyses using the latest versions of SAS, SPlus and StatXact software as needed. The trial will be reported according to the CONSORT standards for reporting cluster-randomized trials [43]. The results will be expressed as odds ratio [OR] (for binary outcomes), hazard ratio [HR] (for time-to-event outcomes) or mean difference (for continuous outcomes), with corresponding standard errors, 95% confidence intervals and associated p-values. P-values will be reported to three decimal places with p-values less than 0.001 reported as p < 0.001. For all tests, we will use alpha = 0.05 level of significance. We will examine residuals to assess goodness-of-fit and model assumptions for all analyses as appropriate.

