## Background

Surgical resection of rectal cancer is the cornerstone of curative therapy. Typically during rectal cancer surgery the tumour and a contiguous segment of normal bowel are removed and the bowel tract reestablished. For surgically treated patients two unfortunate outcomes are permanent colostomy and local tumor recurrence. For various reasons the operating surgeon may deem it necessary to remove the rectum and anus rendering the patient dependent on a permanent colostomy. Local tumor recurrence is defined as tumour that recurs in the pelvis near the previous operative site [1-3]. It is especially feared since this outcome is usually inoperable and patients, as a result, can suffer a slow, painful death. This study is testing if these two important outcomes, rates of permanent colostomy and local tumour recurrence, can be improved at the hospital level using the surgeon-directed Quality Initiative in Rectal Cancer (QIRC) strategy.

Studies on rectal cancer surgery outcomes usually show that rates of permanent colostomy, local tumour recurrence, and even patient survival vary markedly at the surgeon, hospital, or region level. For example, among the regions of Ontario, Canada researchers showed that rates of permanent colostomy following rectal surgery varied from 31% to 41% [4]. A study examining local tumour recurrence among surgeons operating in five hospitals in Edmonton, Alberta showed that rates varied from 10% to 45% based on surgeon specialty training and procedure volume [5]. These Canadian results are similar to studies in Europe [6-8]. The presence of important outcome variations suggests variation in the quality of delivered surgery.

Total mesorectal excision is a refinement of traditional surgical techniques that stresses sharp dissection of the mesorectum – the lymph node-bearing portion of the rectum – with careful autonomic nerve preservation [9-11]. There are a growing number of single institution series describing improvements in outcomes with the introduction of total mesorectal excision- in particular local tumour recurrence rates as low as 5% and permanent colostomy rates of 10–15% [12-18]. Population based studies from Europe also detail positive changes when surgeons in large areas adopt total mesorectal excision principles [19,20].

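### The primary model adjusts for adjuvant therapies received after randomisation and leaves surgical pathology open as a covariate, so it need not estimate the strategy's total effect

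*Protocol article*

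**What the plan says.** All of the relevant wording is in the Analysis section of the protocol article.

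- **Primary model.** It states that "the primary outcomes of colostomy rate and local recurrence rate will be assessed using a nested (cluster) analysis model", and that this model will consider "the correlation of outcomes within each hospital, and the influence of covariables". Covariate adjustment is therefore part of the primary analysis.
- **Covariate list.** "Treatment arms will be compared with respect to potential covariates using continuous and categorical univariable analyses". The list covers patient, treatment, tumour and hospital variables, among them "treatment (adjuvant therapies), tumour (stage, node counts, margin status, other histology measures". The next sentence reads "Methods of analysis, including adjustment for covariates, will use the cluster randomization trial design". Nothing limits adjustment to variables fixed before randomisation.
- **The one adjustment singled out.** "Adjustments for adjuvant therapies are especially important since it is likely these treatments will not be delivered among centers using a standard regimen".

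Three other sections matter. Randomization says that patients were accrued as soon as their site had been randomised. Background says that total mesorectal excision "stresses sharp dissection of the mesorectum – the lymph node-bearing portion of the rectum", and the interventions aim to change how surgeons do this. Primary objective asks whether the strategy lowers hospital rates of the two outcomes.

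**The concern.** The objective is a total effect: what happens to hospital rates when surgeons are exposed to the strategy, by whatever route. Every patient, operation, pathology report and course of adjuvant therapy comes after hospital randomisation. If the strategy, or the surgical result it produces, influences who receives adjuvant therapy, a model that holds adjuvant therapy constant estimates something other than that total effect. The same applies with more force to margin status and node counts, which are products of the resection the strategy tries to change.

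Analysing hospitals in the arm to which they were randomised does not cure this, because the departure comes from the conditioning and not from the allocation. At stake is the odds or hazard ratio that will be read as the answer to the primary question.

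**Working it through.** **1. Order of events.** Site randomised → patients accrued → operation → pathology. Any pre-operative therapy falls between accrual and operation, and any post-operative therapy falls after the operation. The article does not say which kind its adjuvant therapies are. In either case they are received after randomisation.

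**2. The planned effect.** Sample size gives local recurrence of 20% (control) and 8% (intervention).

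Total OR = (0.08/0.92) / (0.20/0.80) = 0.348; ln = −1.056.

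**3. Method.** Take a binary covariate C with prevalence q in an arm and odds ratio R for recurrence. For each arm, solve for the intercept a in

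(1 − q)·expit(a) + q·expit(a + ln R) = total risk (0.20 or 0.08).

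The arm odds ratio conditional on C is exp(a₁ − a₀). The share of the effect removed is 1 − ln(conditional OR)/(−1.056). All values of q and R below are assumptions.

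**4. Adjuvant therapy.** Assume R = 0.5 and 50% use in control.

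| Use in intervention arm | Conditional OR | Share of log OR removed |
|---|---|---|
| 30% | 0.302 | −13% (effect looks larger) |
| 40% | 0.321 | −8% |
| 50% | 0.343 | −1% |
| 60% | 0.368 | 5% |
| 70% | 0.396 | 12% |

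Check of the last row. Control risks are 25.4% without and 14.6% with therapy (average 20%). Intervention risks are 11.9% and 6.3% (0.3 × 11.9% + 0.7 × 6.3% ≈ 8%). The OR without therapy is (0.119/0.881)/(0.254/0.746) ≈ 0.396.

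**5. Margin status, if it enters the model.** Conditional OR:

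| Positive margins, control / intervention | R = 2 | R = 3 | R = 5 | R = 8 |
|---|---|---|---|---|
| 15% / 10% | 0.359 | 0.364 | 0.366 | 0.361 |
| 15% / 5% | 0.376 | 0.394 | 0.419 | 0.442 |
| 20% / 10% | 0.374 | 0.389 | 0.407 | 0.420 |
| 20% / 5% | 0.391 | 0.422 | 0.467 | 0.514 |
| 25% / 5% | 0.406 | 0.450 | 0.518 | 0.595 |
| 10% / 10% (no improvement) | 0.345 | 0.340 | 0.328 | 0.309 |

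Where margins improve, the range is 0.36–0.60, so 3% to 51% of the log odds ratio is removed. With no arm difference nothing is removed. The small move away from 1 in the last row arises because a conditional odds ratio differs from a marginal one even without mediation.

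**6. Permanent colostomy.** The outcome definition says that it is usually known at surgery. For those patients, pathology and post-operative therapy follow the outcome, so they cannot confound it. A minority with a temporary stoma are classified up to 18 months later. For them, post-operative therapy can precede the outcome, but it still follows randomisation. The article describes one modelling approach for both outcomes and makes no distinction here.

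**The case against.** Four points deserve weight.

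**Only adjuvant therapy is named for adjustment.** A reader might infer that the primary model will adjust for margin status, node counts and stage. The text calls these potential covariates on which arms are compared, and the model's covariate set is not itemised. Their entry is possible, not stated, and a final list may properly sit in an analysis plan that is not shown. This point stands. What remains is that the article positively fixes adjustment for adjuvant therapy and does not rule out the pathology variables.

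**No selection rule is stated.** A reader might also infer that covariates will be chosen according to whether the arms differ on them. The article says that the arms will be compared, not that the result decides what enters.

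**Not all of these variables follow from the operation.** Tumour extent largely pre-dates surgery, and only nodal staging depends on what is resected. Pre-operative therapy precedes the operation. This stands, but such therapy is still post-randomisation, and the article does not separate it from post-operative therapy.

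**The plan has a reason.** Regimens vary among centres, and Data gathering says that radiation is given at a small number of regional cancer centres. Variation can therefore arise outside the strategy and fall unevenly across 16 hospitals. That is a fair reason for a sensitivity analysis. It does not justify a primary adjustment: chance differences between hospitals are covered by randomisation and the clustered variance, and differences caused by the strategy belong to its effect.

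**Conclusion.** The point holds in this form: the primary model is committed to adjustment for a post-randomisation treatment and leaves surgical pathology open as a covariate, so it need not estimate the total effect named in the objective.

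On assumed inputs, adjuvant adjustment shifts the planned odds ratio of 0.35 to between 0.30 and 0.40, a modest change of unpredictable sign. Margin adjustment, if used and if margins improve, gives 0.36 to 0.60. The documents supply no rate of adjuvant use or positive margins and no covariate effect, so these figures show direction and scale only. No colostomy shift was computed.

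Two stronger conclusions are not supported. Adjustment does not necessarily shrink the effect: for the one adjustment the text fixes, the shift can go either way. Nor do the documents show that an effective strategy would be found ineffective. An adjusted odds ratio of 1.0 needs the whole effect to run through margins, for example positive margins of 25% versus 5% with recurrence of 65% if positive and 5% if negative (0.25 × 65% + 0.75 × 5% = 20%; 0.05 × 65% + 0.95 × 5% = 8%). Those values are chosen to produce that result.

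**What to change.** For both primary outcomes, define the primary contrast as the arm effect from the clustered model. Leave it unadjusted, or adjust it only for pre-specified characteristics that the strategy cannot alter and that the Analysis section already lists: age, sex, comorbidities, weight and height, hospital teaching status and procedure volume. Report adjuvant therapy, margin status, node counts and pathological stage by arm as process measures. Keep models containing them, and label them sensitivity or exploratory analyses.

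This changes wording only and needs no new data; it should be settled before outcomes are analysed. The price is that chance imbalance in adjuvant or pre-operative therapy across the 16 hospitals is addressed in a sensitivity analysis and not in the primary model.

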#### Secondary objective

We wish to test if the QIRC strategy can lead to improved quality of life, and improved bladder, bowel, and sexual function among patients surgically treated for rectal cancer. We hypothesize that patients treated in hospitals exposed to the QIRC strategy (intervention) will have higher scores on quality of life measures, and bowel, bladder and sexual function questionnaires compared to patients treated in control arm hospitals.

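### The named model for quality of life and function is a nested analysis of variance with no baseline term, although baseline scores are collected; a baseline-adjusted nested model would be more precise

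*Protocol article*

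**What the plan says.** All references are to the protocol article.

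- **Data gathering:** the secondary scales were "measured at four times: baseline (pre-operatively or within 4 weeks of surgery) and at 6, 12 and 18 months post-surgery".
- **Analysis, secondary outcomes:** "Secondary analyses will be conducted on bowel, bladder and sexual function, and quality of life using nested analysis of variance". The sentence names no covariate, no time structure and no role for the baseline score.
- **Analysis, covariates in general:** "Methods of analysis, including adjustment for covariates, will use the cluster randomization trial design". This clause is not limited to the primary outcomes.
- **Analysis, variables listed as potential covariates:** "This will include patient (age, sex, comorbidities, weight and height), treatment (adjuvant therapies), tumour (stage, node counts, margin status, other histology measures", followed by hospital teaching status and volume. No quality-of-life or function score is listed.
- **Analysis, primary outcomes:** these "will be assessed using a nested (cluster) analysis model that will consider the correlation of outcomes within each hospital, and the influence of covariables". The secondary sentence has no matching phrase.
- **Analysis, effect measure:** "mean difference (for continuous outcomes), with corresponding standard errors, 95% confidence intervals and associated p-values".
- **Secondary objective:** intervention patients "will have higher scores on quality of life measures, and bowel, bladder and sexual function questionnaires compared to patients treated in control arm hospitals".
- **Secondary outcomes:** surgeons decide which patients may be candidates for these measurements, and consent follows. The size of this subset is not given.
- **Randomization:** 16 hospitals, blocked 1:1, not stratified by volume or teaching status.

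**The concern.** The trial pays for a baseline measurement of every secondary scale and then names a model family that, in its ordinary meaning, has no continuous covariate. An analyst who follows the sentence as it stands would leave each patient's starting score out of the arm comparison.

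Two things are at stake. The first is precision: with 8 hospitals per arm the standard error of a mean difference is already large, and a correlated baseline is a cheap way to reduce it. The second is comparability of the patients measured. Hospitals were randomised, but patients enter this part of the study only when a surgeon who knows the arm puts them forward. A difference in starting scores between arms therefore need not be chance alone, and a model without the baseline score does nothing about it.

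**Working it through.** **No figure to reproduce.** The article gives no sample size, standard deviation, intracluster correlation (ICC), baseline correlation, effect size or power for the secondary scales. The only inputs taken from it are 8 hospitals per arm, two-sided alpha 0.05, and 336 / 8 = 42 patients per hospital for the primary outcomes. Everything else is assumed.

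**Assumptions, central case.** m = 21 consenting patients per hospital (half of 42); ICC = 0.02; true difference d = 0.30 SD; one follow-up time. The baseline correlation is r_p at patient level and r_h at hospital level.

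**Formula.** In SD-squared units:

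Var = 2 × [ICC × (1 − r_h²) + (1 − ICC) × (1 − r_p²) / m] / 8

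Power comes from the noncentral t with noncentrality d / √Var. Degrees of freedom are 14, or 13 when a hospital-level baseline term is fitted.

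**Without baseline.** Var = 2 × (0.02 + 0.98/21) / 8 = 2 × 0.06667 / 8 = 0.01667. SE = 0.129, noncentrality = 0.30 / 0.129 = 2.32, power 0.580.

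**With baseline.**

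| r_p | r_h | Var | SE | df | Power | Gain (points) |
|---|---|---|---|---|---|---|
| 0.3 | 0 | 0.01562 | 0.125 | 14 | 0.608 | 3 |
| 0.3 | 0.3 | 0.01517 | 0.123 | 13 | 0.616 | 4 |
| 0.5 | 0 | 0.01375 | 0.117 | 14 | 0.663 | 8 |
| 0.5 | 0.5 | 0.01250 | 0.112 | 13 | 0.699 | 12 |

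With equal correlation r at both levels, the variance is multiplied by 1 − r²: 0.91, 0.75 and 0.51 for r = 0.3, 0.5 and 0.7.

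**Sensitivity.** Over 15 to 42 patients per hospital, ICC 0.01 to 0.04 and d from 0.25 to 0.35 SD, the gain with r = 0.5 at both levels is 3.9 to 11.9 points. It is smallest where power is already high (0.944 to 0.982 at m = 42, ICC 0.01, d = 0.35). The 12 points in the table are therefore the top of this range.

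**If many baselines are post-operative.** Suppose half the patients have a usable pre-operative score and the rest contribute no variance reduction. The patient-level factor becomes 1 − r_p²/2. With r_p = 0.5 and r_h = 0, Var = 2 × (0.02 + 0.04667 × 0.875) / 8 = 0.01521 and power is 0.619, a gain of 4 points. With r_p = 0.3 the gain is about 1 point (0.594).

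**Chance baseline gap.** In the central case its SE is 0.129 SD. At r = 0.5 a one-SE gap moves the unadjusted estimate by 0.5 × 0.129 = 0.065 SD. This movement is already contained in the unadjusted SE of 0.129, so it is another view of the precision loss and must not be added to it.

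**The case against.** The strongest reply is that the defect is read from silence. One sentence names a model family for several instruments, and a condensed article may leave covariate terms and the repeated-measures structure to a fuller document. The general covariate clause comes before the outcome-specific sentences and could cover a baseline score. The listed variables are not presented as a closed set. A nested analysis of variance with time as a factor could also use the baseline through an arm-by-time contrast.

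Much of this stands, and it rules out four stronger readings that a reader might infer:

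- *The plan excludes the baseline score.* Nothing says so; it is simply not named.
- *The hypothesis compares raw scores.* The Secondary objective states a direction only, which adjusted means would satisfy equally well.
- *The baseline is averaged into the arm effect.* That would follow only if all four times entered as outcomes and only the main effect of arm were used. The article does not say how time enters.
- *A chance baseline gap biases the result.* It does not. An unadjusted comparison of randomised clusters is valid for chance imbalance, and its SE already carries that gap. Only a systematic gap from surgeon referral would be bias. It cannot be quantified from the document, and adjusting for the measured score would correct it only in part.

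It is also fair that these are secondary outcomes for which no power is claimed, and that every input to the calculation is assumed.

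What the reply does not remove is that the article names a specific method. It lists potential covariates without the one most likely to predict the outcome, and it mentions covariables in the model sentence for the primary outcomes only. That is a stated choice with a better alternative that uses data already collected.

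**Conclusion.** The point holds in limited form. The only secondary model named has no baseline term, and the general covariate clause neither supplies nor forbids one. Followed as worded, the analysis is valid for chance imbalance but less precise than it need be, and it leaves any referral-driven baseline gap uncorrected.

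In the central case the gain from adjustment runs from about 3 to 12 power points, depending on the assumed correlation and the level at which it acts. It falls to about 1 to 4 points if half the baselines are unusable and the correlation acts within hospitals only. These figures illustrate the scale and are not estimates for this trial. The primary outcomes and the trial's sample size are untouched.

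**What to change.** In the Analysis section, replace the nested analysis of variance for the secondary scales with a hospital-nested analysis of covariance, fitted as a linear mixed model:

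- outcomes: scores at 6, 12 and 18 months;
- random effects: hospital and patient;
- fixed effects: arm, time and arm-by-time;
- covariate: the same scale's pre-operative score;
- inference: adjusted mean difference with 95% confidence interval, using hospital-level degrees of freedom.

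The baseline window, "Quality of life and bowel, bladder, and sexual function were measured at four times: baseline (pre-operatively or within 4 weeks of surgery"), can be read to include scores taken after the operation. Such scores may already reflect the intervention, and adjusting for them could remove part of the effect. They should not serve as the covariate. Handle them as missing through the multiple imputation already planned. A missing-indicator term is the weaker choice, because patients enter through surgeon selection after randomisation and the pattern of missing scores may differ by arm.

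The cost is a short change of wording, no new data, and at most one hospital-level degree of freedom. The downside is a smaller gain where few pre-operative scores exist.
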